### 7.2. Secondary outcomes - binary

Where the outcome of interest is binary, comparison by treatment group will be examined using a binary logistic regression and will be adjusted for factors used in the minimisation algorithm, unadjusted odds ratios will also be presented. In addition the results will be presented as relative risks with 95% CI, calculated from the odds ratio [using methods described by Deeks JJ, Higgins JPT, Altman DG (editors). Chapter 9: Analysing data and undertaking meta-analyses. In: Higgins JPT, Green S (editors). Cochrane Handbook for Systematic Reviews of Interventions. Version 5.0.1 [updated September 2008]. The Cochrane Collaboration, 2008. Available from [www.cochrane-handbook.org](http://www.cochrane-handbook.org/).] and absolute risk differences with 95% CI.

1. Modified Rankin score at six-months [mRS 0-2 v mRS 3-6].
2. Death from any cause by six-months.
3. Death from any cause by twelve-months.
4. New diagnosis of depression since randomisation by six-months.
5. New diagnosis of depression since randomisation by twelve-months.

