## 2. Introduction

Fluoxetine Or Control Under Supervision (FOCUS) is a parallel-group multicentre randomised trial to establish the effect(s) of routine administration of Fluoxetine in patients with a recent stroke. The trial aims to recruit at least 3000 patients. Patients are randomised via a web based randomisation system utilising a minimisation algorithm with a random component to receive Fluoxetine 20mg once daily or matching placebo capsules for 6 months and follow up at 6 and 12 months.

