## 4. Study Methods

### 4.1. Randomisation and blinding

Having obtained consent, the randomising person collects the baseline data necessary to complete a randomisation form and enters the patient’s baseline data into our computerized central randomisation service by means of a secure 24/7 Web interface or a telephone call to the trial office during office hours. After the computer program has checked these baseline data for completeness and consistency it allocates that patient a unique study identification number and a treatment pack number which corresponds to either Fluoxetine or Placebo. The system applies a minimisation program to achieve balance for four factors:

- Delay since stroke onset [2 – 8 days v 9 – 15 days]
- Predicted outcome at 6 months based on Counsell 2002 [predicted probability of being alive & independent at 6 months of 0 – 0.15 v 0.16 – 1]
- Presence of a motor deficit [yes v no – where deficit is NIHSS5 (right or left) >0, NIHSS6 (right or left)>0 or NIHSS7 >0]
- Presence of aphasia [NIHSS question 9: 0 v 1 – 3 ]

The minimisation algorithm randomly allocates the first patient to a treatment, but allocates each subsequent patient to the treatment that leads to the least difference between the treatment groups with respect to the prognostic factors (Altman 2005). To ensure that we retain a random element to treatment allocation, patients will be allocated to the group which minimizes differences between groups with a probability of 0.8. The system contains a list of treatment codes for each centre and which match the stocks held at that centre. At the end of the session each patient is allocated a treatment code which corresponds to either an active (f.luoxetine 20mg once daily) or placebo treatment pack which contains six months supply of capsules held at that centre. The randomisation system will take account of the drug stocks held locally to firstly ensure the allocated treatment is available and second to minimise wastage.

The patient, their families, the healthcare team including the pharmacist and anyone involved in outpatient assessments will be blinded to the treatment allocation.

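### SAP 7.2 derives relative risks from an unspecified odds ratio; if the adjusted one is converted at the observed placebo risk, the relative risk moves away from 1

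*SAP*

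**What the plan says.** Section 7.2 covers five binary outcomes: mRS 0-2 against 3-6 at six months, and death and new depression, each by six and by twelve months. For all of them, "comparison by treatment group will be examined using a binary logistic regression and will be adjusted for factors used in the minimisation algorithm". The unadjusted result is a supplement: "unadjusted odds ratios will also be presented".

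The next sentence adds two further measures. Relative risks come by conversion: "In addition the results will be presented as relative risks with 95% CI, calculated from the odds ratio", with a methods handbook cited for the calculation. Then come the absolute measures, "and absolute risk differences with 95% CI", for which no method is given.

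The adjustment set is in section 4.1: "The system applies a minimisation program to achieve balance for four factors". These are delay since onset, predicted outcome, motor deficit and aphasia. Predicted outcome is the modelled probability of being alive and independent at six months, split at 0.15. That is nearly the same event as the first outcome listed in 7.2.

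The SAP does not say which of the two odds ratios is converted, or which control risk enters the conversion.

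**The concern.** The odds ratio from a covariate-adjusted logistic model is conditional: it compares patients who share the same covariate values. The proportion with the event in the placebo arm is marginal. Odds ratios are non-collapsible, so when the covariates are prognostic and treatment has an effect, the conditional odds ratio lies further from 1 than the marginal one, even with perfect balance. Putting the conditional odds ratio and the marginal placebo risk into one conversion formula gives a relative risk that describes neither the population nor any stratum, and that lies too far from 1.

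Relative risks and risk differences are the figures that clinicians read most easily. An exaggerated relative risk for independence would make a benefit or a harm look larger than the trial showed. It could also disagree with the risk difference printed beside it, because the two would imply different event rates on fluoxetine. Leaving the choice of odds ratio and control risk open also leaves it to be made after the results are known.

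**Working it through.** The SAP gives no figure on this point, so there is none to reproduce. The check asks how far the converted relative risk can lie from the marginal one.

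**Inputs from the SAP.** Adjusted logistic model, relative risk by conversion from an odds ratio (7.2); predicted outcome as a binary adjustment factor (4.1).

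**Assumptions, not in the SAP.** Stratum sizes, stratum risks and the treatment odds ratio. The two-stratum cases use a single prognostic factor.

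**Formulas.**
- Treated risk in a stratum with control risk p and conditional odds ratio OR: OR·p / (1 − p + OR·p).
- Marginal risks p0 and p1: averages over the strata. True marginal RR = p1/p0.
- Converted RR = OR / (1 − p0 + p0·OR).
- Inflation = (converted RR − 1)/(true RR − 1) − 1.

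**Main case: mRS 0-2, 45% of patients at 8% independent, 55% at 60%, OR 1.30.**
- p0 = 0.45×0.08 + 0.55×0.60 = 0.366.
- Treated risks: 0.104/1.024 = 0.1016 and 0.78/1.18 = 0.6610.
- p1 = 0.45×0.1016 + 0.55×0.6610 = 0.409.
- True RR = 0.409/0.366 = 1.118; risk difference 4.3 points.
- Converted RR = 1.30/(0.634 + 0.366×1.30) = 1.171; implied risk difference 0.366×0.171 = 6.3 points.
- Inflation = 0.171/0.118 − 1 = 45%. The RR itself is off by 1.171/1.118 − 1 = 4.8%.

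**Same case, opposite direction, OR 1/1.30 = 0.769.** Treated risks are 0.063 and 0.536, so p1 = 0.323 and the true RR is 0.882. The converted RR is 0.769/(0.634 + 0.366×0.769) = 0.840. Here the converted value is too low.

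**Range at OR 1.30: 35-50% in the poor stratum, 5-10% independent there, 50-65% elsewhere.**
- Smallest inflation (35% at 10%, 65% at 50%): p0 = 0.360, true RR 1.143, converted 1.173; 21%.
- Largest (50% at 5%, 50% at 65%): p0 = 0.350, true RR 1.102, converted 1.176; 74%.
- Over the whole range the true RR is 1.10-1.15 and the converted RR 1.14-1.20. The true risk difference is 3.6-5.2 points and the implied one 5.5-6.6.

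**Milder separation: 40% at 15%, 60% at 45%, OR 1.30.** p0 = 0.33, p1 = 0.384, true RR 1.163, converted 1.183; inflation 12%.

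**Rarer outcome: half at 5%, half at 15%, OR 1.30.** p0 = 0.10, p1 = 0.125, true RR 1.253, converted 1.262; inflation about 4%. With assumed overall risks of 8-14% and separation of this order or less, it is about 0-4%.

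**Cross-check with four independent binary factors.** Assumed prevalences were 0.40, 0.50, 0.87 and 0.29, with p0 from 0.08 to 0.63 and conditional OR from 0.5 to 2.

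| Assumed covariate odds ratios | Inflation of RR − 1 | Largest error in the RR itself |
| --- | --- | --- |
| Weak (1.2, 2, 1.5, 1.2) | 0.6-3.8% | 1.6% |
| Moderate (1.3, 4, 2, 1.5) | 2.0-14.4% | 5.4% |
| Strong (1.5, 10, 3, 2) | 4.6-38.9% | 11.6% |

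The table excludes OR 1, where the error is zero. In every scenario, converting the unadjusted odds ratio at the same p0 returned the true marginal RR exactly.

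**The case against.** A reader might infer that the SAP commits to converting the adjusted odds ratio at the overall placebo risk. It does not: it reports both odds ratios, writes only of the odds ratio, names no control risk, and leaves the formula to a handbook that is not at hand. On the unadjusted reading with the observed control risk, nothing is wrong. This stands, and the point is therefore conditional. The adjusted reading is still the more natural one, since the adjusted model is the stated comparison and the unadjusted odds ratio an addition to it.

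A reader might also infer that every relative risk is overstated. That is true only for odds ratios above 1. Below 1 the converted value is too low, and at 1 there is no error.

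The larger percentages need strong separation. The main case implies a stratum odds ratio of (0.60/0.40)/(0.08/0.92) = 17, which no figure in the SAP supports directly. The 0.15 cut-off makes a low risk in the poorer stratum plausible if the prediction is calibrated, but the 50-65% elsewhere is a guess. This stands as a limit on the size, and it is why the milder case is shown.

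One might add that the conversion treats the control risk as known, so its interval is too narrow. At this size that is negligible. With 1500 per arm and 37% against 40%, the interval is 0.987-1.178 by conversion and 0.987-1.184 directly.

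Finally, these are extra displays of secondary outcomes. No test, sample size or primary result depends on them.

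**Conclusion.** The point holds in conditional form and is minor. Section 7.2 does not fix which odds ratio or control risk gives the relative risk, and its most natural reading pairs quantities that do not belong together.

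For mRS 0-2 the effect on the relative scale could be exaggerated materially: by 45% in the main case, 21-74% across the wider assumed range, and about 12% with milder separation. As a ratio of relative risks the same errors are modest, 1.17 against 1.12 in the main case.

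For death and new depression, at assumed risks of 8-14% and modest separation, the inflation is about 0-4%. It would be larger if the factors predicted those outcomes strongly: the strong four-factor set gives 10% at a risk of 8% and an odds ratio of 1.25 (1.226 against 1.205).

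None of the stratum sizes, risks or covariate strengths comes from the SAP, so these figures show a plausible scale, not an expected error. The direction, the zero error at the null and the exactness of the unadjusted conversion do not depend on them.

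**What to change.** In section 7.2, replace the conversion from the odds ratio with two statements.

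1. Adjusted relative risks and risk differences are obtained by standardisation from the fitted adjusted logistic model. Predict each patient's risk with everyone set to fluoxetine and then to placebo, average each, and take the ratio and the difference, with delta-method or bootstrap 95% confidence intervals.
2. Unadjusted relative risks and risk differences are taken directly from the 2x2 table.

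Each pair then implies the same event rates, and nothing is left to choose after unblinding. The section should also say which category of the dichotomised mRS counts as the event, because a relative risk depends on that choice.

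The cost is a change of wording, slightly more analysis work in standard software, and adjusted relative risks somewhat closer to 1 than the conversion would give. Both odds ratios stay as planned.

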### 6.3. Success of minimisation, and baseline data

**Minimisation**: Check minimisation is successfully balancing on minimisation factors.

**Other baseline data [collected on randomisation form]:** Check treatment balanced by sex, ethnicity, whether patient is an inpatient, depression, diabetes, previous CHD, previous ischaemic stroke/TIA, previous intracranial bleeding, history of GI bleeding, hyponatraemia, bone fractures, current mood [both yes, 1 yes, none yes], recent intracerebral bleeding, type of stroke/OCSP classification and total NIHSS.

**Other data collected post treatment [collected on discharge form]:** Check the following are equally balanced by treatment group: final diagnosis of randomising event, post randomisation non-trial medication, discharge destination and in-hospital compliance variables for inpatients [received any trial medication, taking till death/discharge, reasons for not taken till death or discharge and doses missed].

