### 7.4. Secondary outcomes - continuous

Where the outcome of interest is continuous, these will be compared between treatment groups using linear regression adjusting for factors in the baseline minimisation, or an alternative approach as necessary. This analysis will be conducted for the following outcomes at both six and twelve months.

1. Quality of life as measured by the EuroQol [EQ-5D]
2. Depression and anxiety as measured by the mental health inventory 5 [MHI-5 – question 21,22 of 6-month follow up; question 17,18 of 12-month follow up] and SIS [question 14 on 6-month follow up; question 10 on 12-month follow up].
3. Fatigue as measured by the vitality sub-scale of the Short Form (36) Health Survey [SF-36 question 20 on 6-month follow up; question 16 on 12-month follow up].
4. Limb strength as measured by SIS [question 12 on 6-month follow up; question 8 on 12-month follow up].
5. Hand function as measured by SIS [question 18 on 6-month follow up; question 14 on 12-month follow up].
6. Cognitive function as measured by SIS [question 13 on 6-month follow up; question 9 on 12-month follow up].
7. Communication as measured by SIS [question 15 on 6-month follow up; question 11 on 12-month follow up].
8. Extended ADL as measured by SIS [question 16 on 6-month follow up; question 12 on 12-month follow up].
9. Mobility as measured by SIS [question 17 on 6-month follow up; question 13 on 12-month follow up].
10. Social activity as measured by SIS [question 19 on 6-month follow up; question 15 on 12-month follow up].
11. Overall patient outcome as measured by the SIS total score
12. Overall recovery as measured by SIS thermometer [question 28 on 6-month follow up; question 24 on 12-month follow up].

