### 7.6. Pre-specified sub group analysis

Comparison of mRS at 6-months based on Ordinal analysis will be split by the following sub-groups: age [<70, ≥70], baseline probability of being alive and independent at 6-months [<0.15, 0.16-1 based on Carls model], type of stroke [ischaemic, haemorrhagic], patient able to provide own consent [yes, no] adjusting for baseline motor impairment [yes/no], baseline aphasia [yes/no] and baseline depression [yes/no].

Motor impairment: In patients with motor impairment resulting from the initial stroke [where motor impairment is defined as above] is there a difference in the motor function at 6 months [as measured by SIS, question 12, 17, 18 on follow up)]. Is this maintained at 12 months? Linear regression analysis will be performed on the baseline to 6-month change and separately for the 6-month to 12-month change both unadjusted and also adjusted for factors in the minimisation.*.*

Communication impairment: In patients with communication impairment resulting for the initial stroke [where communication impairment is defined as above on NIHSS] is there a difference in the communication function at 6 months [as measured by SIS, question 15]. Is this maintained at 12 months? This analysis will be performed unadjusted and also adjusted for factors in the minimisation.

Linear regression analysis will be performed on the baseline to 6-month change and separately for the 6-month to 12-month change both unadjusted and also adjusted for factors in the minimisation.

Mood: Is there a relationship between outcome [as defined by mRS at 6-months] and mood [measured using MHI5] and is this relationship affected by Fluoxetine?

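### The mood outcomes are adjusted only for the four minimisation factors, although depression and current mood are recorded at entry; adding them would cost almost nothing and recover some precision.

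*SAP*

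**What the plan says.** Section 7.2 lists "New diagnosis of depression since randomisation by six-months" as item 4, and the twelve-month version as item 5. For every outcome in that section the comparison "will be adjusted for factors used in the minimisation algorithm, unadjusted odds ratios will also be presented".

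Section 7.4 item 2 covers depression and anxiety, measured by MHI-5 and by a SIS question, at six and twelve months. The model is "linear regression adjusting for factors in the baseline minimisation, or an alternative approach as necessary". The alternative is not described and names no covariate.

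Section 4.1 defines the minimisation factors: "The system applies a minimisation program to achieve balance for four factors". They are delay since onset, predicted probability of being alive and independent, motor deficit and aphasia.

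Section 6.3 shows what else the randomisation form holds. It includes depression, in the list that begins "Check treatment balanced by sex, ethnicity, whether patient is an inpatient, depression, diabetes", and "current mood [both yes, 1 yes, none yes". There the two items serve only as balance checks in the DMC report.

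Section 7.6 adjusts the mRS subgroup comparisons for covariates that include "baseline aphasia [yes/no] and baseline depression [yes/no". The schedule in section 4.2 places MHI-5 and SIS at weeks 26 and 52 only.

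**The concern.** A baseline measure of the same construct is usually among the strongest predictors of a later score. Here no such score is taken, so the two randomisation-form items are the only entry information on mood that the SAP shows. The plan uses one of them for mRS, where it is likely to predict less, and neither for the outcomes it should predict best. Minimisation does not balance them, so a chance difference between arms in entry mood passes straight into the adjusted mood comparisons.

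Mood is not peripheral in this SAP. Section 3 asks whether any benefit is mediated by mood, and 7.6 has a separate mood analysis. Wider intervals than necessary on MHI-5 and new depression weaken the answers to those questions.

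**Working it through.** **Inputs.** The SAP gives no power, effect size, SD, depression rate or baseline-outcome correlation for the mood outcomes, so there is no figure of the plan's own to reproduce. The only documented number is the target of at least 3000 patients (section 2), taken as 1500 per arm on the assumption of equal allocation. Two-sided 5% testing is also assumed. All other inputs below are assumptions and are shown as ranges.

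**1. Continuous outcome (MHI-5).** Let r be the partial correlation of entry mood with later MHI-5, given the minimisation factors. Adjustment multiplies the residual variance by 1 − r² and the standard error by √(1 − r²). The equivalent unadjusted sample is 3000/(1 − r²). Power is for a difference of 0.10 SD and is 78.2% without adjustment.

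| r | 1 − r² | SE factor | SE reduction | 3000 worth | Power |
|---|---|---|---|---|---|
| 0.1 | 0.99 | 0.995 | 0.5% | 3031 | 78.6% |
| 0.3 | 0.91 | 0.954 | 4.6% | 3297 | 81.9% |
| 0.5 | 0.75 | 0.866 | 13.4% | 4000 | 88.5% |

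The upper end is demanding for a yes/no item. If 8% are depressed at entry, the gap in later MHI-5 needed to give r is r/[√(1 − r²) × √(0.08 × 0.92)] within-group SDs. That is 0.3/(0.954 × 0.271) = 1.2 SD for r = 0.3, and 0.5/(0.866 × 0.271) = 2.1 SD for r = 0.5. A more common positive mood answer would need smaller gaps.

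**2. Chance imbalance.** With 8% depressed at entry, the SD of the between-arm difference in that share is √(2 × 0.08 × 0.92/1500) = 0.0099, about 1 percentage point. If depressed patients score 1 SD lower later, a typical imbalance moves the MHI-5 comparison by about 0.01 SD. The standard error of the comparison is √(2/1500) = 0.037 SD.

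**3. Binary outcome (new depression).** Logistic regressions were simulated with and without a binary entry-mood covariate: 3000 patients, 13% risk in control patients without the covariate, treatment odds ratio 0.72, 400 runs per scenario.

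| Share with low entry mood | Odds ratio of entry mood | Power without | Power with |
|---|---|---|---|
| 10% | 2 | 81.8% | 81.8% |
| 10% | 4 | 81.8% | 83.5% |
| 20% | 2 | 87.5% | 87.5% |
| 20% | 4 | 88.5% | 91.3% |

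The gain is 0 to about 3 points. With 400 runs each power has a simulation error of about √(0.82 × 0.18/400) = 1.9 points, so these figures are approximate.

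**4. If cases present at entry were recorded as new.** Suppose a share q is depressed at entry and a fraction f of them is recorded as new equally in both arms. True new depression in the rest is 15% v 11% (relative risk 0.733). The observed risks are (1 − q) × 0.15 + qf and (1 − q) × 0.11 + qf. For q = 5% and f = 1 this gives 0.1925 v 0.1545, a relative risk of 0.803.

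| q | Relative risk, f = 0.25 | Relative risk, f = 1 |
|---|---|---|
| 2% | 0.742 | 0.765 |
| 5% | 0.755 | 0.803 |
| 10% | 0.775 | 0.847 |

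Neither q nor f can be taken from the SAP. The table shows only the direction and the possible spread.

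**The case against.** The strongest defence is that adjusting for the minimisation factors is one prespecified rule applied across outcomes, with unadjusted odds ratios alongside for the binary ones. Randomisation protects the comparison, so leaving out a prognostic covariate is not a validity defect. The entry items are coarse, the gain may be negligible, and chance imbalance is small at this sample size. All of that stands. It limits the size of the point but does not remove it: the data are already collected, and 7.6 shows that the authors consider baseline depression a usable covariate.

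A reader might go further and infer that the plan counts pre-existing depression as new. The document does not support this. The outcome is worded as a new diagnosis since randomisation, which by its terms excludes illness already diagnosed, and section 3 narrows it to depression needing antidepressants. What the SAP lacks is a stated rule for patients depressed or screening positive at entry. Eligibility and ascertainment may be settled in the protocol, which is not at hand. The depression item in 6.3 sits in a list of mostly past conditions and could mean history rather than current illness. Nor would adding covariates reclassify any case; only a restricted analysis bears on that question.

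**Conclusion.** The point holds as a low-cost improvement to secondary analyses, not as an error that threatens a conclusion. Sections 7.2 (items 4 and 5) and 7.4 (item 2) leave out the only entry mood data that the SAP shows. The cost is lost precision and uncorrected chance imbalance, without bias.

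For MHI-5 the loss runs from negligible to material, and which end applies depends on a correlation that the SAP does not give; low to moderate values are the more plausible for such coarse items. For new depression the covariates matter little. Dilution by cases present at entry would pull the relative risk towards 1 if it occurred equally in both arms, but whether it occurs, and how much, cannot be established from the SAP. The primary analysis is unaffected.

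**What to change.** In 7.2 items 4 and 5 and 7.4 item 2, add baseline depression (yes/no) and current mood (none, one or both answers yes) to the adjusted models, alongside the minimisation factors. Provide a missing-category code if any mood answers are absent; section 4.1 says that baseline data are checked for completeness before allocation, so few should be. For the logistic models, state that the adjusted odds ratio is now conditional on the two added items, and keep the unadjusted one.

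As a supporting analysis only, report new depression in patients with no depression and no positive mood answer at entry. This subset is defined by pre-randomisation data, so the comparison remains a randomised one.

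Make the change before unblinding for the final analysis, so that the covariates cannot look chosen from the results. Because the trial statistician sees allocation for the DMC reports, the decision is best taken by the blinded statistician described in 5.2.3. The cost is a few lines of SAP text and one extra table; no new data are needed.
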